### Data collection and monitoring

An independent Data Safety Monitoring Committee will be assembled to assess the safety and validity of the execution of the trial as well as to ensure the best interests of participants will be observed at all times. The committee will be comprised by a chairman, one independent statisticians and two physiotherapists, who will be responsible for (1) monitoring participants’ safety at all times during the trial; (2) noting any reported adverse events, making medical decisions and providing essential management to control the situation; and (3) reviewing participant recruitment and withdrawal and mark down the reasons. Once 10, 50, and 80% of the sample size is reached, a data quality audit will be performed during the trial being conducted. Further, data will be stored in encrypted spreadsheets on secured servers hosted by the West China Hospital of Sichuan University, in which any potential risk of omissions and errors will be regularly scrutinized, and then exported to a statistical software for analysis by a statistician blinded to group allocation. All data collected in this trial will be restricted to the principal investigator and specific members of the research team using the backend of the database or servers. A monitoring committee (The Good Clinical Practice Unit at West China Hospitals) will follow and oversee this trial. The monitor will visit the trial site before trial commencement and, after that, have a visit of the trial site twice per month. The monitor who is in charge will check trial procedures, including the completion rate and quality of prescribed exercises, safety assessments, and data recording, and complete the verification procedures of raw data and participant confidentiality. For the enrollment and follow-up of participants, a trial steering committee will manage the trial process and check day-to-day. Any suspension of participation caused by low adherence or voluntary quit by the influence of the COVID-19 pandemic will be recorded.

### Ethics approval and dissemination

The trial will be conducted in accordance with the Declaration of Helsinki. Ethics approval was granted by the Clinical Trial and Biomedical Ethics Committee of the West China Hospital, Sichuan University (ethics reference: 2021 (1696)). The study was registered on the Chinese Registry website (ChiCTR2200058924). Informed consent will be provided to all participants and signed prior to the trial. All study-related information of subjects will be protected during the trial. On the consent form, participants will be asked if they agree to collect and use of their data should they choose to withdraw from the trial, and this trial does not involve any biological specimens. The consent form is available, on request, from the corresponding author.

The results of this study will be published at local, national, or international rehabilitation conferences and submitted as manuscripts to peer-reviewed journals. The main findings of the study will also be shared with all participants and disseminated to researchers, health service providers, health care professionals, and the public via the courses.

## Discussion

This study aims to investigate the effect of Internet-based power cycling or neuromuscular training on pain and walking function in KOA patients. Unlike traditional research, we enroll eligible participants through outpatient clinic, communities, and the Internet. Our rehabilitation setting will focus primarily on the community. After allocation, we will provide them with health education and a personalized exercise training plan. The entire process will use online video connections and platforms to implement interventions. The exercise process requires community administrators and family members to supervise and provide any support. During telerehabilitation, participants will have opportunities to communicate with their peers in a community setting, thereby promoting willingness and motivation to participate through mutual encouragement [50]. Besides, performing neuromuscular training at home saves patients’ time commuting to hospitals. During this process, community staffs can participate in the professional training of constructing community KOA network rehabilitation to improve the whole-cycle rehabilitation treatment for patients with KOA, which plays an active role in improving community rehabilitation and reducing the burden on individuals and society. The findings of this study may help develop an evidence-based online exercise program to manage symptoms and function in patients with KOA in the community. However, the proposed study also has some potential limitations. First of all, during the implementation of the research plan, participants may not be recruited on time due to the impact of the epidemic, we will expand the online recruitment channels for this. Secondly, there is no evidence-based quantitative tool to record the frequency and details of family members’ companionship during exercise; we will make a patient exercise card-level adverse event table and ask family members and community administrators to make detailed records of the frequency and details of exercise companionship and adverse events.

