### Power cycling group

Participants in this group will conduct three 30-min cycling sessions per week and twelve weeks in total. Participants will perform exercise with power cycling which are set in community before our study launched. Each time participant warms up before exercises and cool down for 5 min after that. The exercise intensity, measured by the rating of perceived exertion (RPE), scores 12–14 points during cycling, that is, with self-efficacy of feeling a little hard [35]. A physiotherapist will supervise participants through a video call weekly, and new exercise prescription will be delivered when participants feel easy or too hard to perform cycling at the pre-set intensity. Doctors and physiotherapists will conduct telerehabilitation assessments, after which they will send exercise prescriptions through applet according to the assessment results. Then, participants scan the QR code typed on the power cycling through the applet to start exercise. If participants have any discomfort during exercise, they can click “End Early” on mobile phone to stop, and the physiotherapist will automatically receive a feedback, and they will decide whether it is necessary to make a new assessment. Besides, the weekly video call session and progressive exercise prescribed by physiotherapist could be considered as a method to monitor potential dropout issue and prevent the loss of follow-up and reduce the number of subjects who violate the allocation plan.

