### Neuromuscular training group

Participants allocated in this group will conduct exercises at home three times per week [36]. Details of neuromuscular training exercises could be found in Table 3 [28]. Generally, it comprises weight-bearing training and up-down stepping exercises. After assessments, doctors and physiotherapists will send training videos to participants and have a video call to ensure the exercises are performed correctly. Family members will accompany the participants during each exercise session (including video call with physiotherapists) to ensure safety and to provide any support. Physiotherapists will prescribe planned exercises according to the feedback received from participants weekly. If pain worsen and could not relieve within 24 h after conducting exercises advanced, participants will be asked to continue the former exercises.

**Table 3 Tab3:** Details of neuromuscular training exercises

	**Exercise dose:** 10 sets/session, 3 sessions/time (with a 30–60-s rest between each session), 3 times/week, 30 min/time, 12 weeks in total	
	**Exercise 1**	**Exercise 2**
Weeks 1–2	**Starting position:** standing, feet shoulder-width apart, and the affected side is holding a fixed table **During exercise:** Unaffected lower extremity keeps straight and slides forward and backward on the flat ground, while the affected side, as a support, flexes at the same time. When the unaffected side slides back, the weight-bearing side extends gradually from the flexion position. Participants are required to keep the alignment of the hip, knee, and ankle alignment and place the center of gravity on the affected side	**Step up:** affected side goes up first, with the center of gravity placed on the lower extremity on the affected side. During the flexion-straight process, the affected side is required to perform as slowly as possible, be kept stable, and avoid shake **Step down:** Unaffected side goes down first. Participants complete the action of descending the steps by controlling the affected side to gradually flex from extension. Being slow, being stable, and avoiding shake like up step exercise are also required

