### Safety measure

Since the majority of the interventions are physical exercises, there is no anticipated harm and compensation for trial participation. Participants will be monitored for any adverse events during the intervention, which will be collected and recorded on the case report form (CRF). All adverse events and abnormal laboratory parameters will be followed up until normal, abnormal clinical significance or return to the pretreatment state.

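### The adverse-event detection routes described are tied to exercise sessions, so any comparison of event rates by arm may be biased upward in the two exercise arms

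*Protocol article*

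**What the plan says.** **Common route.** The Safety measure section covers every arm: "Participants will be monitored for any adverse events during the intervention, which will be collected and recorded on the case report form (CRF". It does not say how events are elicited. The same section states that "there is no anticipated harm and compensation for trial participation", on the ground that most of the interventions are physical exercise.

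**Routes tied to exercise.**
- Discussion, on limitations: the trial will draw up an adverse-event table at the level of the exercise card and "ask family members and community administrators to make detailed records of the frequency and details of exercise companionship and adverse events". The same section describes the role of these people: "The exercise process requires community administrators and family members to supervise and provide any support".
- Power cycling group: "A physiotherapist will supervise participants through a video call weekly". If a participant stops a session early because of discomfort, "the physiotherapist will automatically receive a feedback".
- Neuromuscular training group: "Family members will accompany the participants during each exercise session (including video call with physiotherapists"; physiotherapists also receive weekly feedback, and there is a provision for pain that worsens after a progression.

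**Control group.** Participants take glucosamine capsules. No session, card, companion, video call or automatic signal is described.

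**Contacts shared by all arms.** Common interventions gives every arm education messages three times a week, weekly upload of height and weight, guidance from physical therapists on emotional management, and the option to message healthcare providers. Outcome assessments gives every arm blinded assessments at weeks 4, 8 and 12. Neither section presents these contacts as a question about adverse events.

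**The concern.** Recorded adverse events reflect both how often events happen and how hard the trial looks for them. Here the looking appears uneven by arm. A cycling participant with a sore knee triggers a signal or is seen on a weekly call. A neuromuscular participant has an observer at each session. On what is written, a control participant with a complaint has to raise it, or it has to surface at a contact held for another purpose.

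If events are then tabulated by arm, the exercise programmes could look less safe than the capsule control for reasons unrelated to true incidence, and some events in the control arm could go unrecorded. The Abstract says the trial will establish the feasibility of these programmes in elderly community patients, and readers will look at tolerability when judging that. Uneven detection cannot be repaired in the analysis, because events that were never recorded leave no trace.

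A smaller matter sits beside this. The statement that no harm is anticipated does not fit the protocol's own provisions for discomfort during cycling and for worsening pain in neuromuscular training.

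**Working it through.** The article gives no adverse-event rate and no detection probability, so there is no stated figure to reproduce. The check has two parts.

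**1. Detection routes side by side**

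| Route | Cycling | Neuromuscular | Control |
|---|---|---|---|
| Case report form | yes | yes | yes |
| Applet messages, started by the participant | yes | yes | yes |
| Assessments at weeks 4, 8, 12 (not described as event queries) | yes | yes | yes |
| Weekly physiotherapist contact about the exercise | video call | feedback | none described |
| Automatic early-stop signal | yes | none described | none described |
| Relative at each session | not stated in the arm's section | yes | none described |
| Exercise-card event table, relatives' and administrators' records | yes, by natural reading | yes, by natural reading | not stated; tied to exercise |

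The three shared rows are the same for everyone. Every further row favours detection in one or both exercise arms.

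**2. How large the effect could be**

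Input from the article: 33 participants before a 20% dropout allowance. 33 / 0.8 = 41.25, rounded up to 42, or 14 per arm at 1:1:1. That agrees with the Sample size section and gives 28 exercise participants and 14 controls.

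Assumptions, none from the article: a true participant-level risk p that is equal in all arms; a common route that detects a share c of events in every arm; and session-linked routes that independently detect a share e, in the exercise arms only.

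- Recorded risk, exercise: p × [1 − (1 − c)(1 − e)]
- Recorded risk, control: p × c
- Ratio: [1 − (1 − c)(1 − e)] / c = 1 + e(1 − c)/c, which does not depend on p

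| c | Ratio at e = 0.3 | Ratio at e = 0.6 |
|---|---|---|
| 0.5 | 1.30 | 1.60 |
| 0.7 | 1.13 | 1.26 |
| 0.9 | 1.03 | 1.07 |
| 1.0 | 1.00 | 1.00 |

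Example at p = 0.2, c = 0.5, e = 0.6:
- Exercise: 28 × 0.2 × 0.8 = 4.5 participants with a recorded event
- Control: 14 × 0.2 × 0.5 = 1.4
- With the common route alone, exercise would show 28 × 0.2 × 0.5 = 2.8, so the extra routes add about 1.7 participants

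From two independent binomials at p = 0.2, the probability that the observed exercise proportion exceeds the control proportion is 0.67 at c = 0.5, e = 0.6. It is 0.58 at c = 0.7 and 0.49 at c = 0.9 with the same e, and 0.46 when detection is complete in all arms.

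The expected shift is upward in the exercise arms whenever c is below 1 and e above 0. With 42 participants, the direction seen in one trial is not assured.

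**The case against.** The case on the other side has several parts.

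- **The formal system covers all arms.** This stands. The case report form is the route for every participant, and the Discussion's card and relatives' records add to it. They appear as a remedy for having no tool to record companionship. It would be wrong to infer that adverse events are recorded only through exercise channels.
- **Controls are in regular contact with the trial.** This stands in part. They receive messages, upload data, can write to providers and are assessed three times after baseline. Data collection and monitoring adds a safety committee and a monitor who visits twice a month and checks safety assessments. But no contact is described as asking about events, and the committee notes events that have been reported, so it would inherit any imbalance.
- **Controls are not expressly excluded from the relatives' records.** This stands. All arms receive general exercise advice, and the Discussion speaks broadly of a personalised exercise plan. That controls lack these records is an inference from their being tied to the exercise process.
- **Safety is not an outcome, and no between-arm event comparison is planned in Statistical analysis.** This stands and makes the consequence conditional: it bites only if rates are set side by side.
- **An article leaves the method of eliciting events to the full protocol.** This is fair for missing detail, and no fault is found for that. The point here is that the routes the article does state are asymmetric by arm. Closer watching during exercise is a sensible safeguard; it becomes a problem only when its yield is compared with an arm that is watched less.

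A reader might go further and infer that event rates will be higher in the exercise arms, perhaps by half or more. The documents do not support that. A ratio of that size needs a common route that misses about half of all events, and nothing in the article says whether it does.

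**Conclusion.** The point holds as a risk of differential ascertainment, not as a demonstrated bias. Detection as described is likely to be more intensive in the two exercise arms, so any comparison of event rates by arm may be biased upward there.

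The amount is unknown. On the assumed values above, the ratio of recorded risks at equal true risk lies between 1.00 and 1.60. It is at most 1.07 if the common route finds 90% of events, and exactly 1.00 if it finds all of them. This rests on assumed detection shares, on independence between routes, and on the inference that controls do not have the exercise-linked records.

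The primary and secondary efficacy outcomes are untouched. This is a worthwhile, cheap improvement rather than a defect that threatens the trial. The statement about anticipated harm is a separate wording conflict: the passages need to be reconciled, but the sentence does not show that control participants go unasked.

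**What to change.** 1. At T1, T2 and T3, put the same short adverse-event checklist, with an open question at the end, to participants in all three arms. Use the online assessments already planned, ask it after the outcome measures, and enter the answers on the case report form.
2. State that any between-arm comparison of adverse events uses this source only.
3. Keep the exercise cards, relatives' and administrators' records and early-stop signals for participant safety, and list events from them separately by arm without comparing rates.
4. Reconcile the Safety measure statement on anticipated harm with the discomfort and worsening pain that the two exercise-group sections provide for.

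**Cost.** A few questions at existing contacts, so slightly longer assessments. Answers may reveal allocation to the blinded assessor. Asking last protects the current visit but not the next one if the same assessor returns, so a self-completed form, or a different member of staff for these questions, would be safer. Recall over four weeks will miss minor events. The question and the recall period are the same in all arms, although exercise participants whose events were already noted on cards may remember them somewhat better.

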## Trial status

Recruitment will be started on 1 September 2022, and it is estimated to have a total duration of 10 months. This protocol is the version number 5 dated 2 June 2022.

## Data Availability

Not applicable.

## Abbreviations

OA: Osteoarthritis
KOA: Knee osteoarthritis
IoT: Internet of Things
WOMAC: Osteoarthritis Index Scores from Western Ontario and McMaster Universities
11-NRS: 11-Point numerical pain rating scale
TUG: Timed up and go
6MWT: 6-Min walking test
SF-36: The MOS item short from health survey
OARSI: Osteoarthritis Research Society International
SD: Standard deviation
IQR: Interquartile range
ANOVA: Analysis of variance
QR: Quick response
